### Data management

Data will be collected from RACFs, by research staff. RACF staff will facilitate the collection of data from RACF digital and paper records. Collection of data will be onto a university laptop which is password-protected. Resident’s identifying details (e.g. names and date of birth) will be deleted prior to analysis. Residents will be given a unique study identifier to link data that will be stored in a secure place at the RACF. Data will be entered onto a central database developed with Microsoft Access and stored on the University of Canberra secure and password-protected data storage system. Access to the database will be by the key members of the research team with unique usernames and passwords. The servers are protected by firewalls and are maintained according to best practice. After the completion of the study, the database will remain on the university storage system for 5 years, as per National Health and Medical Research Council (NHMRC) guidelines.

### Statistical analysis

Descriptive statistics will be used to summarise and compare the data at the RACF level in each group at baseline and at the end of the trial, including primary and secondary outcomes as well as additional potential confounder variables (such as demographic profile, duration of residency, presence of dementia, Charlson comorbidity index [59] and number of medical conditions).

Bivariate analyses for group comparisons will use either t tests or ANOVA for data that are normally distributed, Mann-Whitney U and Kruskall-Wallis tests for data that are not normally distributed, or chi-square-based analysis for categorical outcome data. For within group comparisons, paired t tests and repeated measures ANOVAs will be used; if variables are not normally distributed, the Wilcoxon signed-ranks and Freedman tests will be used, while the McNemar test will be used for changes in proportions.

To determine the effect of the intervention on the outcome measures and the changes over time (between-within group effects), multilevel modelling methods, which take into consideration the hierarchical structure of the data (including clustering within RACF and repeated measurement occasions) will be applied. These modelling methods will include mixed-effects generalised linear models (Logistic and Poisson regression models) for binary and count outcomes as well as mixed-effects linear models for continuous outcomes assumed to have a normal distribution, or otherwise transformed to meet the assumption.

Analysis will be weighted by cluster size as required. Interactions and adjusting for demographic characteristics and other potential covariates will be included when deemed necessary. Residents who enter, die or move from RACFs after baseline data collection will have only one data point and will be included in the analysis. When data are missing at random, patterns of missing data will be evaluated, and potential predictors of missing responses will be investigated. Methodological attempts to fill in missing data will be extensively explored and applied as appropriate. These include single imputation approaches (such as regression imputation and nearest neighbours or hot-deck imputation) and multiple imputation approaches. Analysis will be conducted using either SPSS version 26 or STATA version 16. Significance level will be set at the usual 5% alpha-level (two-tailed where applicable). All estimated effects will be reported along with their 95% confidence intervals.

Since the sample size and power calculation have been devised based on the primary outcome and hypothesis, the level of adjustment and number of potential covariates to adjust for may be limited by the sample size and the response rate. Posterior power calculations will be performed based on available sample size and the secondary outcomes.

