### Randomisation and blinding

Randomisation will be at the facility level. RACFs will be randomised into either intervention or control group through computer-generated allocation by an independent researcher external to the research team. Randomisation will be stratified by size of facility. Due to the nature of the intervention, the trial participants will not be blinded.

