### Sample size

It was estimated that a conventional RCT with randomisation of individuals would be able to detect a reduction from 60 to 40% of residents having at least one PIM [14], with a minimum of 106 residents in each arm (total of 212 residents in both arms) with a significance level of 5%, a power of 80% on equal allocation and a response rate of 85%. By adjusting for the loss of power due to clustering, with an intra-cluster correlation coefficient of 0.05 and a cluster size of 93 residents per RACF, the estimated sample size is (1 + [(93–1) x 0.05] =5.6 x 106) or 594 residents in each arm (1188 in both arms), equating to a minimum of 13 sites. The sample size was calculated using G*Power 3.1.9.4 [57].

The estimated prevalence of PIM in RACFs at baseline (60%) was based on previous studies in which the prevalence of PIM in Australian RACF residents were reported as 73% in 2018 [16], 49% in 2014 [14] and 56% in 2012 [58].

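### The simple between-arm tests carry no cluster adjustment: run on residents, the test of PIM status would have a type I error of about 41% at the plan's own ICC, though the multilevel effect analysis is not affected

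*Protocol article*

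**What the plan says.** The Randomisation and blinding section sets the unit: "Randomisation will be at the facility level". The Sample size section allows for this: "By adjusting for the loss of power due to clustering, with an intra-cluster correlation coefficient of 0.05 and a cluster size of 93". It turns these two values into a multiplier of 5.6.

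The Statistical analysis section then has three layers.

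- **Description.** "Descriptive statistics will be used to summarise and compare the data at the RACF level in each group". This is done for both the first and the last time point.
- **Simple tests.** Between arms: "Bivariate analyses for group comparisons will use either t tests or ANOVA for data that are normally distributed". For other types of data the sentence names further tests: "Mann-Whitney U and Kruskall-Wallis tests for data that are not normally distributed, or chi-square-based analysis for categorical outcome data". Within arms: paired t tests, repeated measures ANOVA and their rank-based counterparts, "while the McNemar test will be used for changes in proportions". No unit of analysis and no cluster adjustment is given for any of these.
- **Models.** The intervention effect is assigned here: "To determine the effect of the intervention on the outcome measures and the changes over time (between-within group effects), multilevel modelling methods". On how these models treat the data, the section says: "which take into consideration the hierarchical structure of the data (including clustering within RACF and repeated measurement occasions) will be applied". They cover binary, count and continuous outcomes.

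The section later sets one 5% significance level for the whole analysis without separating the simple tests from the models. It also says that residents who arrive, die or leave after baseline have one data point and are kept in the analysis.

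**The concern.** The between-arm tests named in the second layer are the standard versions, which treat observations as independent. In this trial residents of one facility share prescribers, staff and the allocation itself, and the plan's own sample size treats their outcomes as correlated. A test that ignores this uses too small a standard error and rejects too often.

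The tests are aimed at outcomes, not only at baseline characteristics: the chi-square analysis is named for categorical outcome data, and McNemar for changes in proportions. The primary outcome is the change in the proportion of residents with at least one PIM.

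The within-arm tests raise a separate issue. They compare an arm with itself, so any change over the year that is unrelated to the intervention enters the result. The Discussion itself expects that changes linked to COVID-19 may affect the outcomes. Paired tests also need both visits, so they run on a different set of residents from the one the section says will be analysed.

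At stake is a published p-value from a simple test that appears to support an effect the randomised comparison does not show.

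**Working it through.** **Inputs** (Sample size section unless noted): ICC 0.05; 93 residents per facility; 106 residents per arm before inflation; two-sided 5% level (Statistical analysis section).

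**1. Reproduce the plan's figures.**
- Design effect = 1 + (93 − 1) × 0.05 = 5.6, as stated.
- 106 × 5.6 = 593.6, so 594 per arm and 1188 in total, as stated.
- 1188 / 93 = 12.8, so 13 facilities, as stated.
- For 60% against 40% at 80% power, the usual two-proportion formula gives 97 per arm, or 107 with continuity correction, against the stated 106. This number plays no part in the next step.

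**2. Size of a resident-level test that ignores clustering.** The true variance of the arm difference is the naive variance times the design effect (DE), so the naive standard error is too small by √DE and

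actual size = 2 × [1 − Φ(1.96 / √DE)].

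With DE = 5.6: √5.6 = 2.37; 1.96 / 2.37 = 0.83; size = 0.408, about 41%.

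**3. Sensitivity.** Only the first row uses the plan's ICC and cluster size together. The other ICCs are assumptions, because the article gives no ICC for any other outcome.

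| ICC | Residents per facility | DE | Size |
|---|---|---|---|
| 0.05 (plan) | 93 | 5.6 | 40.8% |
| 0.05 | 91.4 (1188 / 13) | 5.52 | 40.4% |
| 0.05 | 79 (85% of 93) | 4.90 | 37.6% |
| 0.01 (assumed) | 93 | 1.92 | 15.7% |
| 0.02 (assumed) | 93 | 2.84 | 24.5% |
| 0.10 (assumed) | 93 | 10.2 | 53.9% |

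**4. Check by simulation under the null**, 7 against 6 facilities of 93 residents, ICC 0.05: chi-square 41.0%, t test 42.9%, Mann-Whitney 42.0%. A t test on the 13 facility proportions gave 5.0%. The fault therefore lies in the unit of analysis, not in the type of test.

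**5. Which unit does the plan intend?** It does not say. Having at least one PIM is a yes/no status of a resident, while a facility has only a proportion. A chi-square test on PIM status, or McNemar on its change, therefore needs residents as units. The t and Mann-Whitney tests could be run on facility values. Medication-round time and dose-form modification are defined per RACF in the list of secondary outcomes; compared as one value per facility, they carry no such inflation.

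**6. Within-arm tests.** No error rate is derived here. The 5.6 is a cross-sectional figure and need not apply to paired changes. The objection to these tests is the missing control and the loss of residents with one visit.

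**The case against.** The strongest reply is that the plan already analyses the effect correctly. The paragraph after the simple tests gives the intervention effect to mixed models with facility as a level, and the Economic evaluation section uses analogous models for costs. A reader might infer from the 41% that the trial itself has that false-positive rate. The document does not support this: nothing in it says that a simple test decides any outcome. This part of the reply stands.

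A reader might also infer that each outcome will have two contradictory p-values. Two are possible, but whether they would disagree is not known.

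Third, the section opens with comparison at RACF level, and a facility-level test keeps its size. This stands for t and rank tests run on facility values. It does not rescue chi-square or McNemar on PIM status.

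Fourth, the ICC of 0.05 was chosen for the PIM outcome, so the 41% does not carry over to falls, hospital use, dose or anticholinergic score. That is correct, and the range in the table is illustrative for those outcomes.

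Fifth, residents with one data point can enter the multilevel models, so the statement that they are included is not false for the plan as a whole. It fails only for the paired tests.

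Last, a condensed article may leave the ranking of analyses to a fuller document. The absence of a ranking is not the point here. The article itself names tests for clustered outcomes that are invalid when run on residents, and it states no adjustment for them.

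**Conclusion.** Wrong as written, for the simple tests only, and of a severity below must-fix. A resident-level chi-square test of PIM status has a type I error of about 41% instead of 5%, given the plan's ICC of 0.05 and 93 residents per facility. It is about 38% at 79 residents, and about 16% and 24% if the ICC were 0.01 or 0.02. The figure rests on the test being run on residents and on equal cluster sizes. It does not apply to the multilevel models, to outcomes compared as one value per facility, or to the paired within-arm tests. Those paired tests cannot serve as evidence of effect, because they do not use the control arm and they leave out residents seen once.

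**What to change.** In the Statistical analysis section, replace the paragraph on simple tests with wording to this effect:

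- Any simple between-arm comparison of a resident-level outcome is made on facility-level summaries (t test with degrees of freedom equal to the number of facilities minus 2, so 11 with 13 facilities, or a Wilcoxon rank-sum test), or with a cluster-adjusted test.
- Within-arm changes are reported descriptively and are not used as evidence of an intervention effect.
- The between-arm contrast in the multilevel model alone decides each outcome.

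The third item largely makes explicit what the section already implies; the first two are the substantive changes. The cost is analysis wording and fewer small p-values to report. Data collection and sample size do not change.

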#### Primary outcome

Change in proportion of residents who are prescribed at least one PIM (from baseline to 12 months) according to the 2019 Beers Criteria [52]

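### With about 13 facilities and a change outcome, the mixed logistic model named for the primary analysis can exceed 5% type I error unless facility-by-time variance and small-sample inference are built in

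*Protocol article*

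**What the plan says.** Under Randomisation and blinding: "Randomisation will be at the facility level", stratified by facility size. The Primary outcome section gives the endpoint as "Change in proportion of residents who are prescribed at least one PIM (from baseline to 12 months"), judged against the 2019 Beers Criteria. The Sample size section inflates an individually randomised calculation for clustering and arrives at a total "equating to a minimum of 13 sites".

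Under Statistical analysis, effects of the intervention and changes over time are to be estimated by models described as follows: "multilevel modelling methods, which take into consideration the hierarchical structure of the data (including clustering within RACF and repeated measurement occasions) will be applied". Binary outcomes get mixed-effects logistic regression, in SPSS 26 or Stata 16. On error control: "Significance level will be set at the usual 5% alpha-level (two-tailed where applicable"), with 95% confidence intervals throughout. The same section keeps residents who have a single data point in the analysis.

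The levels named are facility and measurement occasion. The random effects are not listed, and the text gives no reference distribution, degrees-of-freedom rule or small-sample correction.

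**The concern.** The effect of interest is a difference between arms in change over time. A facility intercept that is the same at baseline and at 12 months cancels from that difference. If the model has no term letting a facility's level shift between the two occasions, the change is judged only against resident-level noise, although facilities were randomised. Any real facility-specific drift is then missing from the standard error.

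If facility-level variance does enter the contrast, through a facility-by-time effect or because 12-month values are compared directly, it must be estimated from about 13 facilities. Maximum likelihood tends to underestimate a variance component from so few units, and a z reference ignores the uncertainty in it.

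At stake is whether the stated 5% level and 95% coverage hold for the comparison that decides the trial.

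**Working it through.** **The plan's own figure.** Design effect = 1 + (93 - 1) x 0.05 = 5.6. 106 x 5.6 = 593.6, so 594 per arm and 1188 in total. 1188 / 93 = 12.8, so 13 facilities. This reproduces the article, so the design calculation charges the trial in full for facility-level clustering.

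**Inputs.** From the Sample size section: m = 93 residents per facility, ICC = 0.05, 13 facilities (6 v 7). Assumed, because the document does not give them: the correlation of a facility's effect between baseline and 12 months (CAC), 0.8 to 1; and the within-resident correlation (r), 0 to 0.7. The range for r starts at 0 because residents with a single data point lower the effective pairing.

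**Case A: only a constant facility intercept.** On the linear scale, the variance of a facility's change is proportional to ICC(1 - CAC) + (1 - ICC)(1 - r)/m. The model sees only the second term. Hence

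variance ratio V = 1 + m x ICC x (1 - CAC) / [(1 - ICC)(1 - r)], and true type I error = P(|Z| > 1.96/√V).

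Example, CAC 0.95 and r = 0.7: V = 1 + 93 x 0.05 x 0.05 / (0.95 x 0.3) = 1.82. The standard error is too small by a factor of 1.35, and type I error is 15%.

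| CAC | r = 0 | r = 0.5 | r = 0.7 |
|---|---|---|---|
| 1.00 | 5% | 5% | 5% |
| 0.95 | 8% | 11% | 15% |
| 0.90 | 11% | 16% | 23% |
| 0.80 | 16% | 25% | 34% |

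A simulation of facility means (40,000 runs, 7 v 6 facilities) agreed with the r = 0 and r = 0.5 columns. A binary-data simulation (3,000 runs) at r = 0.7 gave 13%, 20% and 32% for CAC 0.95, 0.90 and 0.80, slightly below the formula.

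The article gives reasons to doubt CAC = 1. Its Discussion expects pandemic-related changes in staffing and visiting clinicians that may affect outcomes. Recruitment is staggered, so facilities' 12-month windows cover different calendar periods. Residents also enter and leave.

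**Case B: facility-level variance enters the contrast.** Degrees of freedom = 13 - 2 = 11. P(|t11| > 1.96) = 0.076. The critical value is 2.20, and 2.201/1.96 = 1.12, so the correct interval is 12% wider than the z interval.

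Maximum-likelihood estimation adds to this. Null trials were simulated with 6 v 7 facilities of 93, ICC 0.05, 60% prevalence in both arms and one time point, and analysed by random-intercept logistic regression fitted with quadrature:

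| Test | Rejection rate, separate runs |
|---|---|
| Logistic model, Wald z | 9.3%, 9.5%, 9.8% |
| Same model, t(11) cut-off | 6.8%, 7.1% |
| Facility-level t test | 4.7%, 4.7%, 5.0% |

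With unequal facility sizes (CV 0.4) the three tests gave 10.7%, 7.5% and 4.1%. Changing the critical value alone therefore does not fully restore the level, whereas the facility-level test does not exceed it.

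**The case against.** The strongest reply is that the article states neither a Wald z test nor the omission of a facility-by-time effect. Its wording is compatible with a model that has both remedies. Random-effects lists and degrees-of-freedom methods commonly sit in an analysis plan, which is not shown. This stands. A reader might infer that the primary p-value and interval are already too optimistic as planned, but that reads a specification from silence.

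Four narrower objections also stand:

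- A reader might add the two effects together. They are alternatives: if the facility intercept cancels, underestimating its variance does no harm to the change contrast.
- The 9-10% comes from a single-time-point simulation, not from the repeated-measures model.
- CAC and r are assumptions. At CAC = 1 the level is held, and residents with only one occasion pull the inflation toward the lower end of each range.
- A reader might extend the point to the intervals in the economic evaluation. That evaluation models cost per participant over the trial period, and no calculation was made for it.

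The objection does not dispose of the point. The article does choose a method for the primary effect, a mixed logistic model on as few as 13 facilities. A simple facility-level test holds its level there, while the uncorrected version of that model does not. This is a choice between methods, and not only a request for detail.

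**Conclusion.** The point holds conditionally and should be fixed. Fitted with a constant facility intercept only, the named model has type I error of 5% if facility effects are perfectly stable, about 8-15% at CAC 0.95 and 16-34% at CAC 0.8. Where facility-level variance enters the contrast and z is used, the figure is about 7.6% from the critical value alone, and about 9-10% with maximum-likelihood estimation at a single time point.

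These sizes rest on the article's ICC of 0.05, 93 residents per facility and 13 facilities, on assumed CAC and r, and on a linear-scale approximation for the change contrast. They do not show that the final analysis will be wrong. They show that with so few facilities the validity of the primary test depends on two choices that the article's wording leaves open.

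**What to change.** Preferred: make the primary test a two-stage facility-level analysis of the change, or of the 12-month proportion adjusted for baseline. Refer it to t with facilities minus 2 minus the stratum degrees of freedom, or use a permutation test that follows the size-stratified allocation. The mixed logistic model can then be supportive.

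Alternative: keep the mixed logistic model as primary, add a facility-by-time random effect alongside the resident and facility effects, and name a small-sample degrees-of-freedom method that the software offers for logistic mixed models. Kenward-Roger applies to the linear mixed models planned for continuous outcomes and should not be cited for the logistic one.

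Cost: a few sentences, a little code and no new data. Intervals widen by about 12% against z at 11 degrees of freedom. With one stratum degree of freedom (an assumption, since the number of size strata is not stated) the critical value is 2.228, and 2.228/1.96 = 1.14, or 14% wider.

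As a guide to power, take a plain 12-month comparison of 60% v 40% with 594 per arm. The standard error is √(2 x 0.24 x 5.6/594) = 0.067, and 0.20 divided by the unrounded standard error is 2.97. Power is about 84% with z and 77% with t(11), so part of the apparent power comes from the large-sample reference. Adjustment for baseline may recover some of it.

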## Methods

### Study design

This is a cluster RCT in RACFs in the ACT, Australia, with RACFs as the unit of randomisation. Participating RACFs will be randomised into either an intervention or control group. RACFs in the intervention group, in addition to ‘usual care’, will each employ an on-site pharmacist as member of the healthcare team. RACFs in the control group will continue ‘usual care’ that includes receiving government funded RMMR and QUM services from visiting pharmacists. Intervention and control groups will be recruited and randomised in staggered groups which will run in parallel.

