### Economic evaluation

A within trial cost consequence followed by a cost-effectiveness analysis will be conducted. The cost consequence analysis will explore the incremental impact (compared to the control arm) of the intervention on the disparate secondary outcomes, providing more information to decision makers in addition to a having a focus on the primary outcome. For the cost-effectiveness analysis, effectiveness will be measured in terms of the primary outcome—avoided PIM (reduction of the number of residents who take at least one PIM). A public health sector perspective will be used. All resource use will be valued in 2020/21 Australian dollars without discounting. Total costs for the intervention and control groups will be calculated, as well as average costs per participant, incorporating any additional costs relating to the delivery of the intervention (e.g. additional training, time that a GP spends on reviewing pharmacist recommendations). Resource use captured during the trial will include health service utilisation by each participant (ED visits, hospital admissions, ambulance transfer during the 12 months of control/intervention period; and medications used at baseline and at 12 months). Analogous multilevel modelling described above (controlling for differences in characteristics of participants and RACF clusters) will be used to estimate average cost per participant for both intervention and control groups. An incremental cost-effectiveness ratio (ICER) will be computed by comparing the costs and outcomes of the intervention and control groups. Results will be expressed as incremental cost per incremental reduction in the proportion of residents taking at least one PIM. Mean estimates will be used, and confidence values and sensitivity analysis will indicate the robustness and validity of the results and test any assumptions used. Uncertainty around the ICER will be explored using cost-effectiveness acceptability curves.

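### The size stratum used in randomisation is not committed to the between-arm models, where facility size appears only as an optional weight that a mixed model does not need

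*Protocol article*

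**What the plan says.** Under Randomisation and blinding, the unit and the stratification factor are fixed: "Randomisation will be at the facility level" and "Randomisation will be stratified by size of facility". The number of strata and the cut-points are not given.

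Under Statistical analysis, the intervention effect is to be estimated with "multilevel modelling methods, which take into consideration the hierarchical structure of the data", that is, mixed-effects logistic, Poisson or linear models. Three further sentences bear on facility size and covariates:

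- Weighting: "Analysis will be weighted by cluster size as required". No trigger, model or level of weighting is stated.
- Covariates: "Interactions and adjusting for demographic characteristics and other potential covariates will be included when deemed necessary".
- Limit on covariates: "the level of adjustment and number of potential covariates to adjust for may be limited by the sample size and the response rate".

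The potential confounders listed in that section (demographic profile, length of residency, dementia, comorbidity index, number of conditions) describe residents. Facility size is not among them. The Economic evaluation section does speak of "controlling for differences in characteristics of participants and RACF clusters", but in describing the cost model.

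**The concern.** A factor used to restrict randomisation should normally be in the analysis. Stratifying by size balances size between the arms, so the true sampling variance of the arm difference no longer contains the between-stratum part. A model without the stratum still estimates its error from facilities of all sizes, so its standard error includes that part. The p-value and interval are then too cautious, and the precision bought by the stratification is not fully used. With a minimum of 13 facilities there is little precision to spare.

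The weight raises a second question. A mixed model already gives each facility a weight that reflects its information. A further size weight moves away from that optimum and changes the estimand from something near the average facility to something nearer the average resident. Because the weight applies only as required, the text leaves open which of these the primary result will be.

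**Working it through.** **The plan's own figure.** From Sample size: 106 residents per arm before clustering, ICC 0.05, 93 residents per facility.

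- Design effect: 1 + (93 − 1) × 0.05 = 5.6.
- 5.6 × 106 = 593.6, so 594 per arm and 1188 in total.
- 1188 / 93 = 12.8, so 13 facilities.

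This reproduces, and nothing below changes it.

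**Where the variance of a facility mean lies.** In units of the total resident variance, a facility of size m has mean-variance v(m) = 0.05 + 0.95/m.

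- At m = 93: 0.05 + 0.0102 = 0.0602. The between-facility share is 0.05 / 0.0602 = 83%.
- The optimal weight is 1/v(m): 11.4 at m = 25, 16.6 at m = 93 and 17.9 at m = 161. A more than sixfold range in size gives less than a twofold range in weight.

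**Cost of size weights.** For weights w, the variance of the weighted mean is Σw²v / (Σw)². The article gives no spread of sizes, only the mean of 93 and a 20-bed floor (Participants). I assume 13 evenly spaced sizes from 25 to 161 (mean 93, CV 0.46 with divisor 13). Relative to optimal weights:

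| Weighting | Variance ratio |
|---|---|
| Equal per facility | 1.02 |
| Size weight on resident records inside the random-intercept model (linear approximation, w = 1/(0.05 + 0.95/m²)) | 1.015 |
| Size weight on facility-level means (w = m) | 1.13 |
| Size weight multiplied by the mixed model's own weight (w = m/v) | 1.18 |

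Other assumed size sets with a similar CV move the top figure by a point or so, so I put the range at roughly 1% to 19%. The loss depends on the spread. With simulated sizes (7 facilities per arm), facility-level size weights give 1.02, 1.09, 1.18 and 1.28 at a nominal CV of 0.2, 0.4, 0.6 and 0.8. Size weights on top of the mixed model's weights give 1.03, 1.13, 1.25 and 1.40.

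**Effect of the stratum term.** Let f be the share of between-facility variance that size explains. This is an assumption; the article gives nothing on it. The residual variance ratio, adjusted to unadjusted, is (0.05(1 − f) + 0.0102) / 0.0602. With 13 facilities and a two-level stratum, residual df go from 11 to 10 and the t quantile from 2.201 to 2.228. The ratio of interval widths is √(variance ratio) × 2.228/2.201. For f = 0.3: (0.035 + 0.0102)/0.0602 = 0.75, and √0.751 × 1.0123 = 0.88.

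Type I error and power come from a simulation of facility means: 14 facilities (6 of 120 residents, 8 of about 73), allocation stratified by size, resident variance 0.24, ICC 0.05, two-sided 5%, and a true difference of 0 or of 20 points.

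| f (assumed) | Variance ratio | Interval width ratio | Type I error without / with stratum | Power without / with stratum |
|---|---|---|---|---|
| 0 | 1.00 | 1.01 | 0.051 / 0.052 | 0.81 / 0.80 |
| 0.1 | 0.92 | 0.97 | 0.039 / 0.050 | 0.82 / 0.84 |
| 0.3 | 0.75 | 0.88 | 0.026 / 0.050 | 0.83 / 0.90 |
| 0.5 | 0.59 | 0.77 | 0.011 / 0.049 | 0.84 / 0.95 |

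A separate simulation, also with 14 facilities, gave type I error without the stratum of about 0.047, 0.03 and 0.02 at f = 0.1, 0.3 and 0.5. The direction is the same and the exact level depends on the set-up, so about 0.03 at f = 0.3 is a fair summary.

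**The case against.** The strongest reply is that the article never excludes size from the model. The covariate clause is open, the economic section refers to cluster characteristics within analogous models, and a condensed article may leave the covariate list to an analysis plan. This stands in part. A reader might infer that the weight is used in place of the stratum covariate. The text does not say so, and weighting and adjustment are not alternatives. It also does not say that covariates will be chosen after outcomes are seen; it sets no timing. The full covariate list and the handling of the staggered recruitment groups are ordinary analysis-plan detail and are not part of this point. What remains is that the article states an analysis rule, gives size a role in it, and does not commit to the role that the randomisation calls for.

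A second reply concerns the weights. A reader might infer that size weights on resident records make each facility count by its size squared, so that a few large homes dominate. That holds for a resident-level analysis that ignores clustering. The article plans mixed-effects models, where the loss is the smaller one shown above and may be close to nil. Weighting facility-level summaries by size is also conventional and has a sensible target, the average resident. That is a legitimate choice of estimand, but it should be made openly and not as required.

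Third, omitting the stratum does not create false positives, because the test errs on the cautious side. Stratified allocation also already gives the unadjusted analysis a small power gain when size matters (0.81 rising to 0.84 as f goes from 0 to 0.5), so the benefit of adjusting must be measured against that. The comparison above does so.

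**Conclusion.** The point holds in this limited form. Randomisation is stratified by facility size, and the analysis section does not commit to the stratum in the between-arm models and offers size only as an optional weight.

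Including the stratum is a favourable trade. If size is not prognostic, the interval is about 1% wider and power falls by about a point at most. If size explains 30% of between-facility variance, the interval is about 12% narrower, type I error returns from about 0.03 to 0.05, and power for the 20-point effect rises from 0.83 to 0.90. At 10% explained, the gain is about 3% in width and two points of power.

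The weight brings no precision to the planned mixed models. It costs roughly 1% to 19% in variance, about 13% for facility-level weights, at a size CV of about 0.46, and it moves the target towards residents of large facilities.

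The ICC, mean size, number of facilities and effect are the article's. The size CV, the share of variance explained and the two-level stratum are assumptions. The result is a loss of efficiency and an unsettled target, not a bias or an inflated error rate, and the planned sample size is unaffected.

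**What to change.** In Statistical analysis:

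1. State that the size stratum, as used in the randomisation, enters the primary and all other between-arm mixed models as a fixed effect, whatever the baseline data show. It should not fall under the discretionary covariate clause.
2. Delete cluster-size weighting from the resident-level mixed models. If an average-resident result is wanted, name a size-weighted analysis as a prespecified sensitivity analysis and say at which level the weights apply.

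The cost is wording. Statistically, a two-level stratum takes about 1 of 11 facility-level degrees of freedom, and each further level takes one more. Recruitment, data collection and the target of 1188 residents do not change.
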